## 4.5 Withdrawal and termination of the study

### **Reasons for Withdrawal**

Participants may be withdrawn from the study for any reason at any time:

- The participant or legally acceptable representative withdraws the consent
- The Investigator judges that further participation would have a negative effect on the participant's health
- Participant changes location
- No longer interested
- Inability to continue follow-ups

### **Handling of Withdrawals**

Participants can opt for withdrawal at any time for any reason. Participants will be provided with the following options:

1. Allow to be contacted by telephone for further follow-ups:
  - A: Continue with the collection of measurements by attending to the healthcare center
  - B: Provide an answer to self-reported measurements via telephone.
2. No longer be contacted about the research unless I need to be notified of a safety concern.

Also, participants will be provided on who to contact if there are any questions or concerns that arise after their participation in the study.

In the case participants develop T2DM or GDM, health professionals will ask the participant to return to the healthcare centers for monitoring the disease.

### *Definition of lost to follow-up/drop-outs.*

*When the health professional or peer educator has no news of the participants after 6 months (follow-up assessment), the health professional must take every effort to contact the participant by telephone to determine the reason of missing the follow-up assessment. If no news of the participant for 1 year and/or the participant missed 2 follow-up assessments, the health professional again must make every effort to contact the participant by telephone to establish the reason for the discontinuation of participation, and to suggest the participant comes to an end-of-study visit. If all these attempts to contact the participant fail, the investigator can then declare the participant "lost to follow-up". The investigator should document all these attempts in the corresponding study file.*

### **Termination of Study**

Reasons for termination of the study:

1. Impossible to meet the objectives.
2. Any unforeseen event (force majeure), as insecurity, displacement of the population, epidemic, strike.

If the study is prematurely terminated or suspended, the investigators will promptly inform the sponsors and the regulatory authority(ies) of the termination or suspension and the reason(s) for the termination or suspension. The EC's will also be informed promptly and provided the reason(s) for the termination or suspension by the Sponsor or by the investigator/institution, as specified by the applicable regulatory requirement(s).

## 5. STUDY PROCEDURES

### 5.1 Study/visit schedule

The data collection of this study will be carried out by at least 2 health professionals recruited from each healthcare center (a minimum of 12 health professionals, female if feasible). Previous to the intervention program, health professionals will receive a guideline with standardized procedures for the measurements, to ensure the accuracy of the measurements and high-quality data. **Table 1** describes the schedule of measurements including the demographic characteristics and also the primary and secondary outcomes presented in section 2.1 and 2.2. It includes as well the tool to be used and the person that will assess the measurement.

**Table 1.** Schedule of measurements and tools

|                                                              | Tool                          | Administered by                         | Baseline  | 6 months | 12 months | 18 months | 24 months |
|--------------------------------------------------------------|-------------------------------|-----------------------------------------|-----------|----------|-----------|-----------|-----------|
| Demographics                                                 |                               |                                         |           |          |           |           |           |
| Age                                                          | Close ended questionnaire     | Participant                             | X         |          |           |           |           |
| Marital status                                               |                               |                                         | X         |          |           |           |           |
| Number of children                                           |                               |                                         | X         |          |           |           |           |
| Profession                                                   |                               |                                         | X         |          |           |           |           |
| Smoking status                                               |                               |                                         | X         |          |           |           |           |
| Healthy lifestyle adherence (Primary outcome )               |                               |                                         |           |          |           |           |           |
| Diet and physical activity questionnaire*                    | Closed-ended questionnaire    | Participant                             | X         | X        | X         | X         | X         |
| Anthropometrics                                              |                               |                                         |           |          |           |           |           |
| Height**                                                     | Height measuring board (SECA) | Health professional                     | X         |          |           |           |           |
| Weight**                                         | Digital weight scale (SECA)   |                                         | X X X X X |          |           |           |           |
| BMI**                                                        | Calculation kg/m  |                                         | X X X X X |          |           |           |           |
| Waist circumference**                                        | Constant tension tape         |                                         | X X X X X |          |           |           |           |
| Clinical indicators                                          |                               |                                         |           |          |           |           |           |
| Blood pressure**                                             | OMROM*                        | Health professional                     | X         | X        | X         | X         | X         |
| Glycemia**                                                   | Achat glucometer (SECA)       |                                         | X         | X        | X         | X         | X         |
| Dietary assessment                                           |                               |                                         |           |          |           |           |           |
| Diet diversity**                                             | MDD-W questionnaire           | Health professional                     | X         | X        | X         | X         | X         |
| Physical activity                                            |                               |                                         |           |          |           |           |           |
| Physical activity questionnaire**                            | IPAQ-short version            | Health professional                     | X         | X        | X         | X         | X         |
| Acceptability of community support (only intervention group) |                               |                                         |           |          |           |           |           |
| Agreement scale questionnaire                                |                               | Health professional                     |           | X        | X         |           |           |
| Intervention assessment (only intervention group)            |                               |                                         |           |          |           |           |           |
| Focus groups                                                 |                               | Peer educators and health professionals |           | X        | X         | X         | X         |

Abbreviations: Body mass index (BMI); Type 2 diabetes mellitus (T2DM); Gestational diabetes (GDM) ; Minimum dietary diversity for women (MDD-W) In addition to these measurements, the ANC reports of pregnant women will be requested to the healthcare centers.

\*Primary outcome. \*\*Secondary outcome. †OMRON: Digital automatic blood pressure monitor. ~ 24-hour dietary recall will also be assessed randomly within the 6 month period, this will be performed by the health professional and by telephone. For pregnant women the weight will be compared to the recommended gain weight based on pre-pregnancy BMI, as follows: Underweight (BMI < 18.5): 13-18 kg; Normal weight (BMI 18.5 – 24.9): 11-16 kg; Overweight (25 - 29.9): 7-11 kg; Obese (BMI > 30): 5-9 kg.

## 5.2 Obtaining informed consent

As previously mentioned, health workers will identify women meeting the inclusion criteria and provide information about the study. Women interested in participating and meeting the inclusion criteria will be provided with further details about the intervention program. Consequently, the health workers will present an IC in French or in the local language (Kikongo or Lingala) and ask the potential participants to read it carefully and decide for participation by signing the ICF or refusal, contact involved staff for details if needed, or give it back within the following 2 weeks in case further consultation/time is needed.

To obtain IC of the participants, the IC form template (French version) developed by the ITM will be used stating the following (**Annex 4** for intervention group and **Annex 5** for comparison group):

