## 4. PARTICIPANTS, POPULATION & SELECTION

### 4.1 Settings, selection & recruitment

The study will be carried out in Kisantu health district (ZS Kisantu) encompassing a total population of 202,451 inhabitants. Six healthcare centers (NKANDU 1, KINTANU ETAT, NGEBA, KAVWAYA, KINKOKA, MADIMBA) covering approximately 107,000 inhabitants and sharing an integrated strategy of focused antenatal care (ANC) have been identified as operational/interventional centers. Based on past demographics, a total of 4,200 women per year are expected to be pregnant within the 6 centers population coverage, and of those approximately 92% will attend ANC at least in one occasion. Only a modest proportion of women (25%) are expected to attend the recommended 4 visits to ANC.

Women of reproductive age (pregnant and non-pregnant) will be recruited primarily through the healthcare centers in Kisantu as women attend frequently to healthcare centers due to general consultations for ANC and post-natal care, child monitoring, vaccinations among others. Within the 6 healthcare centers previously stated, health workers will identify women meeting the study legibility criteria and provide information about the study. If not enough women could be recruited via the healthcare centers consultations, informative posters will be displayed in the waiting rooms of the healthcare centers with a contact person for further information. If such posters are necessary and plan to be implemented, the posters will be submitted to the Ethical Committee in DRC and IRB at ITM for review and approval. Also community/village leaders will be approached and asked to encourage women to participate. Women interested in participating and meeting the eligibility criteria will be provided with detailed information about the intervention program, including all the specifics of the informed consent (IC). The recruitment of participants will be performed in 1 month, August 2021.

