#### 4.4 Randomization

We will use matched randomization to ensure that the two groups are balanced in terms of population size coverage and geographical area (urban/rural). This will be performed by manually creating 2 groups, each of 3 healthcare centers, based on their population size coverage and geographical area followed by randomly assign the intervention and comparison group to the 2 balanced groups. The randomization will be performed before the intervention begins and it will be carried out by ITM's staff.

Due to the nature of this research and the impossibility of masking the intervention program, this study will not be blinded. Anyhow, to ameliorate the risk of bias, the cluster randomization design was chosen to avoid contamination of information between the participants per healthcare center.

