### Part 1. Research participant information form

This section will compromise a legitimate description of the purpose of the study, the procedures to be followed whereby detailed information of the activities and examinations that will take place will be provided. Also, it will explain the risks and benefits of participating in the study, as well as the compensation and insurance of the study. The form will also include information regarding privacy and data protection, also it will mention that the study was reviewed and approved by the Ethics Committee of the ITM and the local authorities of DRC. Moreover, study participants (or guardians) will be informed that participation in the study is completely voluntary and can withdraw from the study at any time without any negative consequences. Details regarding the contact person in case of questions will be also given.

This study informed consent is based on individuals capable of giving informed consent. For those unable of giving informed consent, we ensure that a legally authorized representative of this person has given permission and this permission takes account of the participants previously formed preferences and values. Minors (<18 years old) are not allowed to participate in this study. Moreover, this study has requested and obtained the permission of the gatekeeper, in this case Zones de Santé (health district) to enroll clusters (healthcare center) during the field visit happened 1st May – 9th May, 2021. Lastly, no opt-out procedures will be stated as this research does not entail any biological residuals nor other type of remaining material such as audio-recordings.

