As part of evaluating the feasibility of community-based activities but also to assess the intervention perception, focus groups with the participants per healthcare center of the intervention group will be carried out. The focus groups will provide the investigators' information regarding the perception of the intervention as well as identify needs (e.g. including husbands or children) and weaknesses that can be further addressed and improved. The focus groups will take place at each healthcare center of the intervention group every 6 months. All enrolled participants will be invited to participate in this activity by the peer educators and health professionals. Participants will be informed that this activity is completely voluntary, explained that the main objective is to discuss their perception regarding the intervention and to identify needs, weaknesses, and improvement points. Besides, participants will be informed about this activity before signing the ICF, where it will also emphasize that this activity is completely voluntarily, participation will have no impact in other related-activities to the intervention, and answers will remain anonymous. During the focus group, at each healthcare centers, all the attending participants will be divided into groups of a maximum of 10 people. Each group will have at least one moderator, a peer educator and/or healthcare professional, that will guide the questions, encourage discussion, and write down the most salient points of the discussion. The moderator will follow the focus group discussion (FGD) guide (**Annex 8**). After completion of each focus group, health professionals will synthesize this information and share it with the investigators for review.

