### **11.3 Informed consent**

No participant may be enrolled into the study until the Investigator or designee has obtained the written IC form described in section 5.2.

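### Arm-specific consent forms imply that each centre's allocation is known during recruitment, so the women approached and consenting can differ by arm

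*Combined protocol and SAP*

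**What the plan says.** - **Who recruits.** In section 4.1, at the six centres, "health workers will identify women meeting the study legibility criteria and provide information about the study". Section 5.2 adds that "the health workers will present an IC in French or in the local language (Kikongo or Lingala"), after which the woman signs, refuses or takes up to two weeks to decide.
- **What they present.** Section 5.2 gives two versions of the form: "Annex 4 for intervention group and Annex 5 for comparison group". Under Part 1 of the same section, "detailed information of the activities and examinations that will take place will be provided". Focus groups, held only in intervention centres, are also disclosed beforehand (section 5.3): "participants will be informed about this activity before signing the ICF".
- **Order of consent and enrolment.** Section 11.3: "No participant may be enrolled into the study until the Investigator or designee has obtained the written IC form".
- **Timing of the draw.** Section 4.4: "The randomization will be performed before the intervention begins". Recruitment is planned for August 2021 (section 4.1) and the intervention for about September 2021 (section 3.1). Whether the draw comes before or after recruitment is not stated.
- **Masking and safeguards.** Section 4.4 says that "this study will not be blinded" and offers clustering as protection against information passing between participants. I found no common consent form, no recruiter unaware of allocation, no rule for approaching women consecutively and no log of women approached or refusing.
- **Outcome and analysis.** The primary outcome is the woman's own answers, recorded by a health professional (section 5.3). The model in section 8.3.3 names no covariates, and section 8.3.2 only compares and tests baseline data.

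**The concern.** In a cluster trial the centres are randomized but the women are recruited one by one. Randomization makes the women comparable only if recruitment does not depend on the allocation. Here the two offers are very different: individual and group education, exercise sessions, goal setting and a pedometer on one side, and basic individual education at baseline on the other (section 3.1). Participants receive no compensation (section 11.6), so the programme is a main reason to join. If staff and women know what the centre will deliver, the intervention centres may enrol women more ready to change their habits, and the comparison centres a different mix. The trial could then attribute to the programme a difference that comes from who was enrolled, or miss a real effect if the selection runs the other way.

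**Working it through.** **Step 1: what the consent procedure requires.** The form exists in two versions, it describes what will be done, and it must be signed before enrolment. The person presenting it works at the centre. To hand over the right version, that person must know the centre's arm. Disclosing the focus groups before signature requires the same knowledge.

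**Step 2: what the timing rule allows.** A draw at any time before the intervention starts satisfies section 4.4, including one before the August recruitment. One draw assigns two pre-formed groups of three centres, so it settles all six arms at once. Nothing in section 4.4 prevents the order that the two forms imply.

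**Step 3: is there room for selection?** Each centre needs 48 women (section 4.3). The six centres cover about 107,000 inhabitants and about 4,200 pregnancies a year, or 4,200 / 6 = 700 pregnancies per centre on average, besides non-pregnant women. Eligibility criteria limit who may enter but do not determine who among the eligible is approached or agrees.

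**Step 4: what the analysis would remove.** The model uses baseline and follow-up scores. If the effect is the group-by-time term, a score difference present at baseline and constant over time largely cancels. Differences in motivation, readiness to change or pregnancy mix that affect change or dropout do not, and no adjustment for them is prespecified.

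**Step 5: scale, under assumption only.** The plan's own precision can be reproduced from section 8.4: 40 evaluable women per cluster, three clusters per arm, ICC 0.1, SD 7, a 6-point difference, one-sided 0.05.
- Design effect = 1 + (40 − 1) × 0.1 = 4.9.
- Effective number per arm = 120 / 4.9 = 24.5.
- Standard error of the difference = 7 × √(2 / 24.5) = 2.00 points.
- Power = Φ(6 / 2.00 − 1.645) = 0.912, matching the stated 91%.

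Let b be a shift, in points, left in the estimated difference after any use of baseline. Then type I error = Φ(b / 2.00 − 1.645), and power for a true 6 points = Φ((6 + b) / 2.00 − 1.645). The values of b are assumptions, and the documents support none of them over another.

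| Assumed b (points) | One-sided type I error | Power for a true 6 points |
|---|---|---|
| −3 | 0.001 | 0.442 |
| −2 | 0.004 | 0.639 |
| −1 | 0.016 | 0.804 |
| 0 | 0.050 | 0.912 |
| +1 | 0.126 | 0.968 |
| +2 | 0.259 | 0.991 |
| +3 | 0.442 | 0.998 |

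The table shows how sensitive the test would be to a residual shift. It does not estimate one.

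**The case against.** The strongest reply is that the plan never says the draw precedes recruitment. That stands: the order is an inference from the two forms. Nor can it be said that women answer the baseline questionnaire knowing their arm. The text of Annexes 4 and 5 was not available to me, so I cannot tell whether a woman learns that another programme exists; she would know what her own form offers.

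Health workers are told to identify women who meet listed criteria, not to pick whom they like. That is fair, but without a consecutive-approach rule or a log, selective approach would be neither prevented nor visible, and refusals would depend on the offer in any case.

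Four stronger readings are tempting and not supported:
- **A size for the bias.** Assuming a 0.2 to 0.4 SD difference in motivation gives 1.4 to 2.8 points at SD 7, or 23% to 47% of the 6-point target. Nothing in the documents supports that range or its direction, and a constant difference would largely cancel as described above.
- **Too few centres.** Systematic differential recruitment is not averaged out by any number of centres. Three per arm matters for chance imbalance, which is a separate issue.
- **The cluster design removes concealment.** Early disclosure does that. The same clusters could be recruited before the draw.
- **Biased self-report at follow-up.** This comes from the open design and would persist under a common form.

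A common form also has a price: comparison women learn of the other programme in a trial clustered to avoid contamination. A general description limits this but does not remove it.

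**Conclusion.** The point holds as a risk that the plan creates and does not guard against. Followed as written, the consent procedure implies that centre staff know the arm while recruiting, and women learn what their arm offers before deciding. The women enrolled can therefore differ by arm in ways that the planned analysis may not correct. It does not follow that comparability is lost, or that the result would favour the intervention.

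The size and direction are not estimable from the documents. The conclusion rests on two assumptions: that the forms differ in what they describe, as section 5.2 indicates, and that they are used at the centres as that section sets out. The correction is worth making because it is cheap and recruitment is already scheduled before the intervention.

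**What to change.** **Section 4.4.** Replace the timing rule with one placing the draw after recruitment and baseline are complete in all six centres. Sponsor staff hold the single draw until then.

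**Sections 5.2 and 5.3.** Replace the two forms with one common consent form that describes both programmes in general terms and mentions possible focus groups. Give arm-specific details at the first programme contact after the draw. Individualized education belongs to both arms (Annex 3), so it need not reveal the arm if given earlier; the pedometer explanation, which is for the intervention group only, would wait. If comparison women receive their education at the baseline visit, no later programme contact is scheduled for them, so the plan should say when they are told.

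**Useful addition.** Log women approached, eligible and refusing by centre. If recruitment has already taken place, report the actual order of draw, consent and baseline, give those counts where records exist, and prespecify any baseline adjustment before database lock.

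**Cost.** One merged form resubmitted to the ethics committees. Peer-educator training, planned for August 2021, is given to all centres or moved after the draw. The September start may slip slightly, because women may take two weeks to return consent and the draw waits for the last baseline. Comparison women learn in general terms that another programme exists.
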